### Intervention

The theoretical basis for the exercise intervention was gleaned from current literature and guidelines from the American College of Sports Medicine (ACSM) and American Diabetes Association (ADA) [25, 26]. Eligible participants will take part in an educational practice period (4 sessions) at the University of Colombo strength gymnasium 2 weeks prior to start of the intervention proper. These sessions will assist participant familiarization with the environment, teach them skills techniques, assess tolerance to the frequency and intensity of exercises etc. Participants will start with minimum tolerable intensity, duration/repetitions and slowly progress to the required exercise dose (AT: 60–70% of HR _max_ for 75 min, RT: 7 exercises all repetitions maintaining 50% repetition maximum (RM) using correct technique). Once participants achieve the minimum requirement, as assessed by the principal investigator, they will start the intervention proper. Pre-intervention (i.e., baseline) parameters will be measured one week before starting the intervention proper (see Fig. 3).

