### Screening

Screening will be undertaken via a thorough medical history and physical activity readiness questionnaire (PAR-Q) [24] followed by a physical examination conducted by a qualified medical practitioner. The objective is to exclude any condition mentioned in the exclusion criteria and ensure safety for progressive exercise. Eligible participants will be allocated to one of the groups and complete a 2D Echocardiogram and Exercise/Stress electrocardiogram/ECG supervised by a consultant cardiologist. Patients who fail the test will be excluded from the study and referred for specialist care (see Fig. 2).

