### Outcome measures

All outcomes are measured pre- (within one week before the start date of the intervention) and post-intervention (within one week after the intervention) (Table 1).

**Table 1 Tab1:** Outcome variables and measuring instruments/procedures

Outcome variable	Measuring instrument/procedure
Anthropometry: Height, weight, body circumferences (waist, hip, mid-arm, mid-thigh)	∙ISAK guidelines. ∙Stadiometer, electronic weighing scale and measuring tape (SECA, Germany)
Body fat %	∙Seven site skin fold measures by ISAK and ACSM guidelines. ∙Harpenden skin fold caliper.
Total and regional body composition	∙Dual energy X- ray absorptiometry (DXA) full body scan. Hologic Discovery W, DXA system.
Cardiovascular endurance/Fitness	∙6 min walk test (6MWT). ∙Queens College/McArdle Step test. ∙Exercise Electrocardiogram (ECG).
Muscle strength	∙ACSM guidelines. ∙One repetition maximum (1RM) testing with machine and free weights (Precor, USA).
Blood pressure	OMRON digital blood pressure monitor (Japan).
Heart rate	Polar heart rate monitors.
Biochemical parameters: Glycemic control (HbA1c FBS, Fasting insulin), lipid level, liver enzymes, HsCRP.	Venous blood samples with overnight fast tested in tertiary care independent laboratory.
Quality of life	SF-36 quality-of-life outcomes questionnaire. Self-administered.
Liking and wanting for different types of food	Computer-based behavioral procedure Leeds Food Preference Questionnaire (LFPQ).Self-administered.

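### Baseline is measured after allocation and after the exercise arms have begun supervised practice, so any early response is absorbed into baseline and the comparison with control is pulled towards no difference

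*Protocol article*

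**What the plan says.** Allocation comes first. Under Screening, after the history, PAR-Q and physical examination: "Eligible participants will be allocated to one of the groups and complete a 2D Echocardiogram and Exercise/Stress electrocardiogram/ECG supervised by a consultant cardiologist".

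Practice comes next. Under Intervention: "Eligible participants will take part in an educational practice period (4 sessions) at the University of Colombo strength gymnasium 2 weeks prior to start". The start meant here is that of the main programme. In these sessions participants begin at the lowest intensity they tolerate and work upwards: "slowly progress to the required exercise dose (AT: 60–70% of HR". The AT target is a 75-minute session, and RT has a separate target. The main programme begins on a judgement, not on a fixed date: "Once participants achieve the minimum requirement, as assessed by the principal investigator, they will start the intervention proper".

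Baseline comes last. The same section says: "Pre-intervention (i.e., baseline) parameters will be measured one week before starting the intervention proper". Outcome measures repeats the timing as a window: "All outcomes are measured pre- (within one week before the start date of the intervention) and post-intervention (within one week after the intervention".

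The control section says that this arm receives standard care, with no specific exercise instruction, and completes all pre- and post-intervention measurements. The primary outcome is the absolute change in HbA1c. The analysis is a linear mixed model for repeated measures with age and sex as covariates.

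**The concern.** A baseline in a randomised trial should be unaffected by the assigned treatment. Here the exercise arms have already trained under supervision, towards the dose of their own arm, when the first HbA1c, fasting glucose, insulin, strength and walking values are taken. Whatever those sessions achieved is subtracted from the change. Controls lose nothing comparable, so a true benefit of AT or RT over control is understated. The AT-versus-RT comparison is affected only as far as early response differs between the two modes.

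The exposure before baseline is also not fixed. The start of the main programme depends on reaching a minimum requirement, and baseline is timed backwards from that start. A participant who needs longer may have trained more before baseline. No analysis can later recover a pre-training value that was not measured.

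**Working it through.** **Sequence.** Read together, Screening, Intervention and Outcome measures give: allocation; stress ECG and echocardiogram; practice towards the AT or RT dose; baseline; main programme. The dose named for each arm confirms that allocation is already known during practice. No text shown reverses this order.

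**Sessions before baseline.** Inputs: 4 practice sessions starting 2 weeks before the main programme (Intervention) and 2 sessions per week (pilot section and both arm descriptions).
- Baseline exactly one week before the start: 1 week of practice × 2 = 2 sessions.
- Baseline at the end of the one-week window: 2 weeks × 2 = 4 sessions.
- Total supervised sessions: 12 × 2 + 4 = 28. Shares: 2/28 = 7% and 4/28 = 14%.

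These shares count sessions, not effect. Early practice sessions start at low intensity, so their share of the training dose is smaller.

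**The plan's own sample size.** Sample size gives 30 per group for 80% power at 0.65 SD and alpha 0.05, and 38 with drop-out. With n = 2(z_α + z_β)²/d² per arm:
- One-sided: 2(1.645 + 0.842)²/0.65² = 29.3, so 30.
- Two-sided: 2(1.960 + 0.842)²/0.65² = 37.2, so 38 before any drop-out.
- 30/(1 − 0.20) = 37.5, so 38.

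The article does not state sidedness, and the stated 30 is reproduced one-sided. Both cases are shown below; the timing point does not depend on which was meant.

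**Illustration of what a loss would do.** Two assumptions are not in the documents: that 0.65 SD is the effect of all 28 sessions, and that a fraction f of it has accrued by baseline. Then d = 0.65(1 − f), and power = Φ(d√(n/2) − z_α) for one exercise arm against control.

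| f | d (SD) | n = 30, one-sided | n = 38, two-sided |
|---|---|---|---|
| 0 | 0.65 | 80.9% | 80.9% |
| 5% | 0.62 | 77.2% | 76.8% |
| 2/28 (7%) | 0.60 | 75.6% | 74.9% |
| 4/28 (14%) | 0.56 | 69.6% | 68.0% |

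The last two rows take response as proportional to sessions. For HbA1c, which the article itself treats as a long-term measure, the true f is probably below them. Fasting glucose, insulin and fitness tests do not have the same protection.

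**The case against.** Several points on the other side have force.

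- **Figures not shown.** Intervention refers to Fig. 3 for the data collection times, and it might place individual measurements more exactly. This limits precision about 2 versus 4 sessions. The order is nevertheless stated in words in two sections that agree.
- **Control exposure is inferred.** The practice period is described for eligible participants without naming arms. The inference rests on doses being given only for AT and RT and on the description of the control arm. If controls did practise, they would be exposed to exercise, which also departs from standard care.
- **Familiarisation has a purpose.** For 1RM, practice before baseline keeps technique learning out of the measured strength gain. This stands, and simply moving 1RM ahead of all practice would count learning as strength. It supports familiarisation that is equal in all arms, not training in two of three.
- **The bias is conservative.** For a true benefit it runs towards no difference from control and would not by itself create a false one. This stands and limits the seriousness.

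A reader might infer more than the documents support. The loss cannot be sized from the pilot: it had three people per group, HbA1c SDs of 1.1–1.7, and scaling its 4-week changes to 1–2 weeks would need an assumption of linear onset for a slow marker. Nor can it be said that every baseline is affected, since the exercise ECG is also a listed outcome and Screening places it before practice. Nor does the plan adjust for an affected baseline as a covariate, since the only covariates it names are age and sex.

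**Conclusion.** The point holds as a weakness in timing that should be corrected. As written, about 2 and up to 4 of 28 supervised sessions come between allocation and baseline in the exercise arms, which biases the exercise-versus-control change towards no difference. This rests on the stated order and on the inference that controls do not practise.

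The size of the bias is not in the documents. A substantial loss in the primary HbA1c effect is not shown, and the power table is an illustration under stated assumptions. The effect on HbA1c is probably small; the more exposed outcomes are fasting glucose, insulin and fitness measures such as the 6-minute walk and step test. The primary comparison is weakened, not invalidated.

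**What to change.** 1. Complete eligibility screening, including the stress ECG, before allocation.
2. Take the HbA1c and other biochemical, body-composition, anthropometric, questionnaire and fitness baselines in all three arms after that and before allocation, hence before the first practice session.
3. For tests that depend on skill, such as 1RM, give every participant the same brief test familiarisation before baseline.
4. Define the practice period as part of the intervention.
5. Set the post-test at a common interval from allocation in all arms.

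**Cost.** The measurements are the same, taken earlier. The pre-post interval lengthens by about 1–2 weeks. The post-test calendar must allow for practice of variable length, so the plan should state how a participant who needs longer to reach the minimum requirement fits the common interval. Test familiarisation for controls is a small extra visit burden.

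If the full change is not feasible, at least the fasting blood sample should precede the first practice session. The session logs already planned should then be used to report, by arm, how many practice sessions preceded each baseline measurement.

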**Fig. 3 Fig3:**
[figure not shown]
Specific data collection time points in the program

#### RT-intervention group

Participants will follow a supervised progressive resistance training program [26] with each session ~ 60–75 min in duration, 2 times per week for 12 weeks. Duration of each session will be tailored according to the capacity of each individual and progressively accordingly. Exercise duration per week will be approximately 150 min with each session consisting of a warm-up, a resistance training component, and a cool-down phase. There will be a 48-h rest period between each session. With regard to frequency of sessions, a recent review stated there is no significant difference in benefits between 2/week of RT compared to 3/week of RT [27]. The 12-week exercise program will allow adequate time for measurable changes in the group (e.g. muscle fiber hypertrophy typically occurs 6–8 weeks after initiating RT).

The RT phase will target biceps, triceps, pectoralis group, core, quadriceps, hamstring, calf, trapezius, latissimus dorsi and gluteal muscle groups with seven upper body (shoulder press, lateral pull down and biceps curl), lower body (leg press/squat, leg extension, heel lifts,) and core (abdominal crunches starting with pelvic and core muscle activation) exercises. Initial resistance for each exercise will be decided individually by testing strength via 1 repetition maximum/ 1RM [28] and determining maximum weight that can be lifted 8–10 times [17, 29]. The volume of exercise will progress from 1 set of 8 repetitions up to 3 sets (1 × 8 to 3 × 8) and then with increasing resistance according to individual capacity and consistent with the literature [27]. Body resistance, free weights and machines will be used in a circuit manner.

#### AT-intervention group

This group will follow a supervised progressive aerobic training program with exercise intensity progressing up to 60–75% of heart rate max (HR_max_). Heart rate will be measured using Polar heart rate monitors. During the program, brisk walking on the treadmill, stepping up-down, and stationary cycling will be used alternately. Exercise intensity will be progressed according to individual tolerability, graded by HR_max_ and rating of perceived exertion (RPE) using the Borg 6–20 scale. Initially, participants’ workload will be adjusted to achieve 60% of HR_max_ and 8–9/20 RPE for 20–30 min and progressed to 75% of HRmax [29] and 12–13/20 of RPE up to 75 min. Each session will be 75 min in duration, 2 times per week (150 min per week) continuously for 12 weeks with the duration of each session tailored to the capacity of each individual and progressively increased.

#### Control group-active control

This group will be provided with standard care - attending normal clinic visits to a consultant physician prescribing medication and providing general health education. No specific instructions will be provided regarding exercise nor additional information regarding dietary modifications. The group will complete all pre- and post-intervention measurements and participants will be contacted via telephone once every 2 weeks during the 12-week period.

##### Background physical activity

Background physical activity will be assessed in all participants using standard pedometers (Yamax, Digi walker, CW- 600 Japan). Participants will wear a pedometer for 1 full week between weeks 8 and 12 of the intervention, except when showering or sleeping. Background activity is the mean daily total step count for the days the pedometer is worn, excluding steps during scheduled exercise sessions. The International Physical Activity Questionnaire (IPAQ) long version [30] will also be used pre- and post-intervention to assess the physical activity level of participants outside the supervised exercise program. Participants will be advised not to engage in any additional exercise outside the prescribed program during the 3 months.

##### Safety

Participants will be advised about hypoglycemic symptoms during and after the exercise program and about appropriate self-management procedures. Pre- and post-exercise capillary blood glucose will be measured at the initial period and as required to avoid hyper/hypoglycemia during the intervention [31]. Participants with a daily blood glucose level (BGL) exceeding 300 mg/dL or 16.7 mmol/L [17, 26] will not engage in exercise during that day and will be directed to appropriate medical care. BGL less than 100 mg/dL or 5.5 mmol/L [17, 26], will be provided with 15–30 g of glucose and re-assessed by a qualified medical doctor on BGL (< 100 mg/dL) and signs and symptoms of hypoglycemia. They will be allowed to continue/discontinue accordingly. An adequate amount of carbohydrate (glucose) and drinking water will be available to participants during activity to avoid hypoglycemia and dehydration. Blood pressure will be monitored before each session. Emergency drugs and access to hospital will be available in case of an emergency. Special precautions will be taken to prevent injuries and blisters in patients’ feet during the program.

##### Adherence to the intervention

Continuous motivation and advice on adherence to the program will be given during sessions. Standard care in the management of T2DM will be continued and no additional information regarding dietary modifications will be provided. All exercise programs will be prescribed and supervised by a qualified medical doctor (principal investigator). Qualified physiotherapists will be recruited as research assistants to support one-on-one exercise sessions and administration of the study (recruitment of participants, randomization, and completion of questionnaires). Physical training instructors will be available in the gymnasium to provide further support. The principal investigator and exercise supervisors will be trained in clinical exercise prescription.

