### Sample size

Ninety (*n* = 90) participants will be recruited from a roll-in method and allocated to RT group (*n* = 30), AT group (*n* = 30), or CN group (*n* = 30). The sample size was calculated considering the expected change of glycosylated hemoglobin (HbA1c) (primary outcome) of the participants. HbA1c is the main parameter to check long-term glycemic control [14]. Previous studies have reported that structured AT or RT had statistically and clinically significant reduction of absolute HbA1c by about 0.6% [21, 22]. Sample size was calculated to have 80% power to detect a moderate 0.65-SD difference in HbA1c, with an alpha/α value of 0.05. Additional participants will be recruited until the required number is achieved (*n* = 38) per group to account for the estimated drop-out rate of 15–25%.

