### Randomization and blinding

Adaptive covariate randomization will be carried out to minimize allocation bias and balance important covariates among treatment groups, which has been recommended for clinical research with low sample sizes [23]. Staff who are responsible for exercise administering and data collection will be blinded for the randomization process. Blinding of exercise administers and participants to the intervention is not possible in exercise intervention trials, whereas the outcome assessors (trained staff in independent tertiary care laboratories) will be blinded [22]. Data analysis will be done by the first author on a de-identified database.

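### The duties given to the physiotherapist research assistants conflict with the statement that exercise and data-collection staff are blind to randomisation, so a recruiter could anticipate the next arm.

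*Protocol article*

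**What the plan says.** All references are to the protocol article.

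- **Randomization and blinding**, on who is blind: "Staff who are responsible for exercise administering and data collection will be blinded for the randomization process".
- **Adherence to the intervention**, on the physiotherapists' first role: "Qualified physiotherapists will be recruited as research assistants to support one-on-one exercise sessions". The same sentence adds a second role: "administration of the study (recruitment of participants, randomization, and completion of questionnaires".
- **Randomization and blinding**, on the method: "Adaptive covariate randomization will be carried out to minimize allocation bias and balance important covariates among treatment groups". The covariates, any random element and the holder of the allocation are not given.
- **Randomization and blinding**, on open treatment: "Blinding of exercise administers and participants to the intervention is not possible in exercise intervention trials".
- **Sample size**, on entry: "Ninety (*n* = 90) participants will be recruited from a roll-in method and allocated to RT group (*n* = 30), AT group (*n* = 30), or CN group". The section raises this to 38 per group to allow for drop-out.
- **Screening**, on order: "Eligible participants will be allocated to one of the groups and complete a 2D Echocardiogram and Exercise/Stress electrocardiogram/ECG". Those who fail the cardiac tests are then excluded.
- **Process evaluation** says that an SOP for randomisation was developed. Its content is not shown.

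**The concern.** The physiotherapists fall into both groups that the blinding statement covers: they help with exercise sessions, and they handle questionnaires. The duties list nevertheless gives them recruitment and randomisation.

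This matters more here than under a simple random list. With covariate-adaptive allocation, the next arm depends on the earlier allocations and on the new patient's covariates. A recruiter meets the new patient, and session staff see the arms of those already entered. Anyone who can foresee the arm can, knowingly or not, choose whom to enter and when, for example by bringing in motivated patients when an exercise arm is due.

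Selection of that kind would act on the primary comparison of HbA1c. Blinded laboratories protect the measurement, not the make-up of the groups. The planned mixed model adjusts for age and sex, which does not capture motivation or expected adherence. Allocation before the cardiac tests adds a second route, because participants can leave the trial after their arm is known.

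**Working it through.** **1. The two statements side by side.** No figure in the plan is at issue, so this step is a comparison of text.

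| Task | Blinding statement | Duties of the physiotherapists |
|---|---|---|
| Exercise delivery | staff blind to the randomisation process | support one-on-one sessions |
| Data collection | staff blind to the randomisation process | questionnaire completion |
| Recruitment | not mentioned | assigned |
| Randomisation | closed to both groups above | assigned |

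On the ordinary reading, staff who help to administer randomisation are not blind to it.

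**2. How predictable the next arm could be.** This is an illustration, because the article does not give the algorithm.

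- From the article: 3 arms of equal size; N = 3 × 30 = 90, or 3 × 38 = 114 with the drop-out allowance; rolling entry.
- Assumed: k = 2, 3 or 4 independent binary factors, each split 50:50; range-based minimisation; a guesser who knows all earlier allocations and covariates and the new patient's covariates.
- Rule: for each arm *a*, S(a) = Σ over factors of (max − min) of the three arm counts at the patient's level, after adding the patient to *a*. An arm with the smallest S is chosen with probability p (ties broken at random), otherwise one of the remaining arms. If all three tie, the choice is random.
- Guess: an arm with the smallest S. Chance = 1/3 = 33%. Each setting was run 2000 times.

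Share of correct guesses:

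| Factors | N | p = 1 (deterministic) | p = 0.8 | p = 0.7 |
|---|---|---|---|---|
| 2 | 90 | 76.5% | 65.8% | 59.0% |
| 2 | 114 | 76.7% | 66.1% | 59.3% |
| 3 | 90 | 85.5% | 70.7% | 62.2% |
| 3 | 114 | 85.7% | 70.7% | 62.5% |
| 4 | 90 | 89.5% | 72.1% | 63.3% |
| 4 | 114 | 89.6% | 72.5% | 63.6% |

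A smaller run (60 repetitions, N = 114, p = 1) gave 76% with two factors and 86% with three.

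**3. Check on the simulation.** With p = 1, a guess is always right when one arm alone has the smallest S, right half the time on a two-way tie and a third of the time on a three-way tie. At N = 114:

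- k = 2: the minimum is unique in 56.7% of allocations. Accuracy must lie between 0.567 + 0.433/3 = 0.711 and 0.567 + 0.433/2 = 0.784. The result is 0.767.
- k = 4: the minimum is unique in 80.3%. The bounds are 0.803 + 0.197/3 = 0.869 and 0.803 + 0.197/2 = 0.902. The result is 0.896.

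Both results lie inside their bounds. In every setting tried, the guess does clearly better than 33%.

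**The case against.** The strongest reply is that the article never says that allocation is open. It describes no tallies in the recruiters' hands, and it mentions a randomisation SOP that may well provide concealment. An article may leave that mechanism to the SOP. This stands: a reader might infer that allocation is unconcealed, but the documents do not establish it, and the lack of a described mechanism is not itself the fault.

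The physiotherapists are also said only to support sessions and administration. Supporting randomisation could mean sending in a patient's details and passing on an assignment made elsewhere, and the article does not say that one individual recruits, randomises and trains the same participant. That reading is possible, so the statements are better called conflicting as written than strictly irreconcilable. The text does not give that reading, however, and a conflict between two stated roles is not an omission.

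Other people also control entry. The consultant approves recruitment, a pre-intern doctor was recruited for first contact, the principal investigator checks eligibility data against clinic records, and a medical practitioner screens. These steps narrow the scope for selection. They do not stop a recruiter from influencing who enters among eligible patients, or when.

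The percentages rest on assumed settings and on a guesser with complete knowledge, whereas an assistant may see only some participants. They measure how guessable the next arm is, not bias in HbA1c.

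Finally, a reader might infer response bias in quality of life from the questionnaire duty. The documents do not support this. Table 1 lists the "SF-36 quality-of-life outcomes questionnaire. Self-administered" and likewise makes the LFPQ self-administered, and the duties list names no instrument.

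**Conclusion.** The conflict between the two sections is stated in the text and has to be resolved. If the duties list is followed in this open, rolling-entry, covariate-adaptive trial, a recruiter who takes part in randomisation could anticipate the next arm. With two to four balanced binary factors, the best guess would be right about 76–90% of the time under deterministic minimisation and about 66–72% with a 0.8 random element, against 33% by chance. These figures assume the factors, the range method and full knowledge of earlier allocations, none of which the article gives.

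The consequence is a risk of selection bias in the primary comparison that the blinded laboratories and the age and sex adjustment would not remove. It is not a demonstrated bias, and no shift in HbA1c has been estimated. Whether the randomisation SOP already prevents it cannot be judged from the article. The point deserves correction before recruitment because selection at entry cannot be reliably repaired afterwards.

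**What to change.** 1. Under Adherence to the intervention, delete *randomization* from the research assistants' duties, so that the section agrees with Randomization and blinding.
2. Have an existing project member who does not recruit, deliver or observe exercise, or collect data hold the allocation record and run the minimisation with a random element. The independent assessor under Intervention fidelity does not fit, because that person observes classes and reviews the exercise log. The random element lowers predictability but leaves it well above chance, so it does not replace this separation.
3. Release each arm only after consent and completed eligibility, including the echocardiogram and stress ECG, and before the practice sessions begin. Reword Screening to match. Release cannot wait for baseline, because the practice period under Intervention has arm-specific targets and starts two weeks before the intervention, while baseline is measured one week before it.

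The cost is one reassigned task, changes to the SOP and to two sections of text, and a small delay while each allocation is released. No added tests are needed, since eligible participants already undergo the cardiac tests. If the SOP already works this way, only the wording has to change.
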